### Data collection

The timing of data collection for questionnaires, physical measurements and laboratory tests is described in detail in Table 1.

#### Questionnaires

Background information on participants was collected with the baseline questionnaire including information from socio-economic status, smoking, earlier weight development, use of medication and self-reported morbidity.

Physical activity habits were elicited at baseline, 36-37 weeks' gestation and 1-year postpartum. Baseline leisure-time physical activity (LTPA) during a typical week prior to the pregnancy and in the other questionnaires LTPA during a typical week of the previous three weeks was included. The degree of breathlessness (strong, some, none) was used to help the women to determine the intensity of their LTPA because there are indications that the meaning of intensity (hard, moderate, light) may be difficult to understand [53]. Validity and reliability of the physical activity questions were examined in a separate study [54].

Dietary habits were assessed by using a validated 181-item food frequency questionnaire (FFQ) [55]. At baseline, the women were asked questions about their diet during one month prior to the pregnancy, since their diet may have changed due to nausea or vomiting at the beginning of the pregnancy. In the follow-up, the women were asked questions about their diet during the previous month. The FFQ was completed during the OGTT during the trial and the follow-up, except for the second follow-up at 36-37 weeks' gestation when the FFQ was mailed to the participants' homes and it was returned to the nurse at the next visit or to the researchers by mail.

Quality of life evaluation was based on the 15-D, which is a validated instrument on quality of life [56] and visual analogue score (VAS) for perceived health. Perceived health has shown to be important factor in predicting functional capacity and health [57]. The 15 D is based on 15 separate items: ability to be physically active, vision, hearing, breathing, sleeping, eating, communicating, elimination, normal functions, mental health, symptoms and signs, depression, anxiety, vitality and sexuality. 15 D scale can be used as a profile including all variables or as a single index from zero to unity. In the 1-year follow-up study, also the Finnish version of RAND-36 [58] and Beck's depression scale [59] were used.

The use of insulin therapy was included in the questionnaire at 36-37 weeks' gestation.

Workability and factors related to return to work were elicited in the 1-year follow-up questionnaire. The workability questions were adopted from workability index developed in the Finnish Institute of Occupational Health. The index has been shown to predict long-term sick leave among young employees [60].

#### Physical measurements

Maternal anthropometric measures. Information on maternal anthropometric measurements were obtained from the standard maternity card. Pre-pregnancy weight was self-reported.The nurses measured body weight of the women at each study visit during pregnancy and height at the first visit. Total gestational weight gain was calculated based on the pre-pregnancy weight and last measured weight during pregnancy. One year postpartum the women were invited to local maternity clinics or to the UKK institute for weight, waist circumference and blood pressure measurements in order to determine the incidence of metabolic syndrome.

Foetal anthropometric measures. Weight of the newborn and gestational age was obtained from medical records of the delivery hospital or from the maternity card. Details related to delivery and perinatal complications will be received from medical birth registry.

#### Laboratory tests

Blood sample analyses included determination of lipids (cholesterol, HDL-cholesterol, triglycerides, LDL-cholesterol, oxidized lipoproteins) and other biological markers (IGF, IGFBp-3, C-peptide, leptin, adiponectin, para-oxonase, insulin) (Table 1). Medical laboratory technologists from the UKK Institute or from the Centre for Laboratory Medicine in Pirkanmaa hospital district took the blood samples (4 × 10 ml) and performed the OGTT for all participating pregnant women. Specimens are analyzed in analysed at [name]'s laboratory at Georgetown University, Washington DC, USA (IGF-1, IGFBP-3, estradiol, progesterone, C-peptide) and in MCA research laboratory, Turku (leptin, adiponectin, insulin, lipids) and at UKK Institute.

OGTT. OGTT was taken at 8-12 and 26-28 weeks' gestation and 1 year postpartum. Analyses were performed at UKK Institute. OGTT has been shown to be the optimal test for insulin sensitivity during pregnancy [61]. In Finnish health care OGTT is performed for women at risk of GDM 26-28 weeks' gestation, because of the expected benefits of prevention of adverse pregnancy outcome related to GDM. We followed the same timing and conveyed OGTT results to nurses who were in charge for possible further treatment. The standard OGTT was performed by giving Glukodyn^R^, including 75 g glucose in 330 ml water after overnight fasting (8 to 14 hours). The Finnish GDM criteria were used to identify participants with GDM [62,63]. Incremental and total area under curve (AUC) was also calculated based on the blood glucose values at 0, 1 and 2 hours after glucose ingestion. AUC can be used as a measure of glucose exposure and it gives a measure of how much and for how long glucose stays in the blood. A long, low concentration exposure may be as important as shorter but higher concentration. Total AUC is a descriptive factor related to basal blood glucose value, whereas incremental AUC more accurately describe glycemic response to foods [64].

### Adverse events

Adverse events related to recent physical activity were asked by the nurses at four visits with a structured form. The adverse events included were classified as warning signs for exercise termination by ACOG [39], e.g. vaginal bleeding, major contractions, dizziness, headache, chest pain and muscle weakness.

### Cost-effectiveness

Total costs of the trial are calculated by summing up all direct costs and dividing the sum by the number of participants. Cost-effectiveness analysis includes differences in direct and indirect costs between the trial and the control groups. Direct costs include all consultations within the health care sector both in specialized and non-specialized care during the trial period (from baseline examinations until delivery). Hospital days, medications and laboratory cost are also included. Costs for the pregnant women include medications and travelling. Trial costs include trial materials, training the nurses for the counseling and the time used for implementation of the counselling and data collection at the routine maternity care visits. Indirect costs, like productivity loss includes absenteeism from work based on the number of days on sick leave during pregnancy. The evaluation of health outcomes is based on quality adjusted life years (QALY). The QALY is based on the number of years of life that would be added by the trial[65].

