Lifestyle modifications have been shown valuable adjunctive therapy in the treatment of GDM [23]. Moreover, there is encouraging evidence on the impact of lifestyle interventions to prevent the progression of GDM to type 2 diabetes in women with history of GDM [24]. The small trials by Mottola et al. [25] and Hui et al [26] showed promising results in preventing GDM with nutrition and physical activity modification. In our own pilot study (n = 105), pregnant women who had intensified dietary and physical activity counseling at routine maternity clinic visits were able to change their diet to favourable direction and to maintain at least moderate physical activity more often than the women with routine counseling [27,28]. Interestingly, there were no high birth weight newborns in the intervention group, but eight of them (15%) in the control group, suggesting that the intervention may have had beneficial effect on maternal glucose tolerance.

The evidence for the effect of lifestyle modification in preventing GDM will accumulate in the future from ongoing studies by Chasan-Taber et al [29] and Oostdam et al [30] and from our study presented here. The *primary objective *of our trial is to show whether individual counseling on physical activity, diet and gestational weight gain can have preventive effect on the development of GDM. *Secondary objectives of our trial *are to evaluate maternal and child weight development, maternal metabolic changes, and changes in maternal physical activity and dietary habits and quality of life. Cost-effectiveness of the trial is evaluated since the prevention of GDM is important in order to reduce direct health care costs, such as hospital days and surgical procedures and indirect costs due to sick leave during pregnancy. To date no cost-effectiveness studies have been published on the prevention of GDM. The purpose of this paper is to describe the design and the methods of a cluster-randomized controlled trial (RCT) to prevent GDM and its 1-year follow-up.

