
#### Monthly thematic meetings on physical activity

During the primary physical activity counseling visit the participants were offered an opportunity to participate monthly thematic meetings on physical activity including group exercise. The sessions were arranged after the working hours close to the maternity clinics and the women's living area. The purpose of the meetings was to support physical activity counseling by providing the participants social support for behaviour change and by introducing them various ways of being physically active. Sessions consisted of five different themes on a non-stop basis, which were:

Theme 1. Physical activity is worthwhile during pregnancy: the benefits of physical activity, current physical activity recommendations during pregnancy.

Theme 2. Walking is pleasant and effective: putting technique and footwear in order.

Theme 3: More alteration and goals for walking: using pedometers and poles.

Theme 4: Preventing urinary incontinence: pelvic muscles and training.

Theme 5: Integrating physical activity to family life: physical activity after pregnancy.

The dates of all the sessions were informed during the primary counseling visit. The participants were to attend to the next meeting after their recruitment but were eventually able attend to every one of them during the pregnancy. The duration of each session was two hours: 30 minutes for getting acquainted, 30 minutes for the theoretical basis related to the theme and 1 hour for the group exercise related to the theme. In all the sessions RPE was used in assessing the intensity of exercise.

The sessions were instructed by the physiotherapists of local health care centres or private clinics. A week before each meeting a reminder of the forthcoming meeting was transmitted via short message service from the research institute to each participant. A week after the meeting the instructor contacted all the participants by telephone to encourage them to continue with their weekly action plans and to get feedback on the meeting from those who had attended. The instructors were trained and provided with all the material needed for the theoretical and practical parts of the thematic meetings. Also, they were paid for the time needed for the training, for the actual meetings and for making the telephone calls.

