**Figure 3 F3:**
[figure not shown]
**Design and timetable of the study: cluster-randomized controlled trial (RCT), 1-year follow-up and linkage to the medical birth registry**.

*The primary maternal outcome *of the trial is the proportion of women diagnosed with GDM, as assessed by oral glucose tolerance test during 26-28 week's gestation and the weight of the newborn adjusted for gestational age.

*Secondary outcomes *of the trial are gestational weight gain and need of insulin treatment during pregnancy determined at time of possible GDM diagnosis (earliest 26-28th week of pregnancy based on OGTT). Additional outcomes are changes in maternal physical activity (frequency and duration of total and domain-specific leisure time physical activity) and dietary habits (food choices related to the objectives of counselling, fibre intake (g/day) and proportions of saturated, polyunsaturated and total fat of total energy intake), maternal quality of life (profile of 15 health-related dimensions during pregnancy). Direct and indirect costs during pregnancy and the cost-effectiveness of the trial (based on QALYs) are calculated. Changes related to blood lipids (cholesterol, HDL-cholesterol, triglycerides, LDL-cholesterol, oxidized lipoproteins) and other biological markers of fat metabolics (IGF, IGFBp-3, C-peptide, leptin, adiponectin, para-oxonase) are determined both during pregnancy and one-year postpartum.

*The outcomes of the 1-year follow-up study *are maintenance of possible changes in physical activity and dietary habits, incidence of metabolic syndrome based on the International Diabetes Federation criteria [52], perceived workability, quality of life (RAND-36 scale), depression (Beck scale) and proportion of women returning to work after maternity leave.

*Medical birth registry linkage *includes information on perinatal outcomes (complications during pregnancy or delivery, such as pre-eclampsia, cesarean section rate and need for labour induction) and incidence of GDM among non-participants.

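### The stated cost horizon ends at delivery and lists no newborn care, which does not fit the savings the economic analysis is meant to capture

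*Protocol article*

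**What the plan says.** The Cost-effectiveness section defines direct costs as health-care consultations "during the trial period (from baseline examinations until delivery". The next sentence adds further items: "Hospital days, medications and laboratory cost are also included". It states no period for them. Indirect cost is "absenteeism from work based on the number of days on sick leave during pregnancy". The intervention's own costs are listed as follows: "Trial costs include trial materials, training the nurses for the counseling and the time used for implementation of the counselling and data collection".

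The Outcome measurements section states the economic outcome more broadly: "Direct and indirect costs during pregnancy and the cost-effectiveness of the trial (based on QALYs) are calculated". That limit covers direct and indirect costs together. Neither section names a newborn cost item, and neither names surgical procedures.

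The Background gives the reason for the economic analysis. Preventing GDM should "reduce direct health care costs, such as hospital days and surgical procedures and indirect costs due to sick leave during pregnancy". It also describes macrosomia and its health consequences in the children of women with GDM. Outcome measurements makes newborn weight, adjusted for gestational age, part of the primary outcome. The Discussion looks ahead to the programme being shown to prevent pregnancy and perinatal complications cost-effectively.

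**The concern.** The counselling takes place during pregnancy, so its cost falls before the horizon closes. Part of what it is hoped to save comes at or after birth: operative delivery, a longer maternal stay, and care of a large or unwell newborn. A horizon that ends at delivery can record the expense and miss that part of the return.

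Cost-effectiveness is not the primary outcome, but the abstract, Background and Discussion all present it as a main aim. Where the window ends could affect the conclusion about value for money. The wording also leaves room for two analysts to treat the birth admission differently.

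**Working it through.** The article states no cost, QALY or cost-effectiveness figure, so there is nothing to reproduce. The check sets the sections side by side and then illustrates scale.

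**1. Where each item falls**

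| Item | Source | Position relative to the stated horizon |
|---|---|---|
| Nurse counselling time, nurse training, materials | Cost-effectiveness | Counted |
| Consultations up to delivery | Cost-effectiveness | Counted |
| Antenatal hospital days | Cost-effectiveness | Counted |
| Sick leave in pregnancy | Cost-effectiveness; Background | Counted, and the two sections agree |
| Caesarean, birth admission | Background names surgical procedures; the cost list does not | Unclear |
| Mother's days after birth | Cost-effectiveness gives no end date; Outcome measurements says during pregnancy | Outside on the natural reading, but not settled |
| Newborn care | Not listed in either section | Outside |
| Pay of thematic-meeting instructors | Monthly thematic meetings section: "they were paid for the time needed for the training, for the actual meetings and for making the telephone calls" | Incurred, but not named among trial costs |

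**2. Nurse time inside the window** (allocated times from Intervention and Counseling on gestational weight gain)

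- Physical activity: (20 to 30) + 4 × (10 to 15) = 60 to 90 minutes
- Diet: (20 to 30) + 3 × (10 to 15) = 50 to 75 minutes
- Weight gain: 5 × 5 = 25 minutes
- Total: 135 to 190 minutes per woman, scheduled before delivery

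This is allocated time. The Control group section says routine care already includes some dietary and physical activity counselling, so the increment over control is smaller by an unknown amount.

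**3. Illustration of the omitted saving**

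Let K be the extra post-delivery cost of mother and newborn per GDM case. K is an assumption, because the article gives no unit costs. With the effect in Power calculations and sample size (40% in control clinics, 24% in trial clinics):

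Uncounted saving per woman = (0.40 − 0.24) × K = 0.16 × K

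| Assumed K (currency units) | Uncounted per woman |
|---|---|
| 0 | 0 |
| 500 | 80 |
| 1,000 | 160 |
| 2,000 | 320 |
| 5,000 | 800 |

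The formula takes the planned effect as real and routes the saving through GDM only. If K is 0, or the intervention does not change post-delivery costs, the horizon introduces no bias.

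**The case against.** **Grammar.** The time limit in Cost-effectiveness closes the sentence on consultations, and hospital days follow with no limit of their own. A reader might infer that post-delivery hospital days and the caesarean are scored at zero. The text does not establish that. The caesarean happens at delivery, and the hospital-days sentence is open-ended. This stands. However, Outcome measurements restricts all costs to pregnancy, so the looser reading sets the two sections at odds, and newborn care is unlisted on either reading.

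**Direction.** A reader might also infer that every intervention cost is counted and that the bias therefore runs only against the intervention. The documents do not support this. The paid instructors of the thematic meetings are not named among the trial costs, and leaving them out would favour the intervention. The understatement of savings is itself conditional on a post-delivery effect. Both limits stand.

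**Choice of perspective.** Outcome measurements places both costs and the 15-dimension quality-of-life profile in pregnancy, so a maternal, pregnancy-only analysis is coherent in itself. The Background does not mention newborn costs when it lists the expected savings, and it does not say that the hospital days are postpartum. Adding newborn costs while health effects remain maternal creates a mismatch that would have to be declared. This has force, but such an analysis could not support the Discussion's aim concerning perinatal complications or cost any consequence of the newborn primary outcome.

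**Condensed article.** Itemised resource use is commonly left to the full protocol or analysis plan. That is a fair answer to a request for unit costs or item lists. It does not answer this point, because the article fixes a horizon and that horizon does not fit its stated purpose.

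**Conclusion.** The point holds in limited form. The stated horizon closes at delivery, omits newborn care, and leaves the birth admission, the caesarean and the post-delivery stay unclear. It therefore excludes or leaves in doubt a main route by which the intervention is expected to save money.

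If the intervention lowers post-delivery costs, as the trial hypothesises, this truncation understates the saving by 0.16 × K per woman at the planned effect. That is 160 units for each assumed 1,000 units per GDM case, and 80 to 800 over an assumed 500 to 5,000. The true size cannot be computed from the article. The net direction over all cost items is also undetermined, because the instructor payments may be missing from the other side of the account. The primary clinical comparison is unaffected.

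**What to change.** In Cost-effectiveness and Outcome measurements:

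- Define one cost window for all items. It should include the birth admission (mode of delivery and maternal hospital days) and newborn hospital care, and end at a fixed postpartum point. Six weeks is convenient because Table 1 already schedules the 15D there.
- Name the thematic-meeting instructor payments (training, meetings, telephone calls) among the trial costs.
- Show newborn costs as a separate line, so that the reader can see the result with and without them beside maternal QALYs.
- Keep the to-delivery window as a sensitivity analysis.

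The cost is a wording change plus some extraction. The Physical measurements section already draws newborn data from delivery-hospital records or the maternity card, and the birth registry supplies caesarean rate and perinatal complications. The article does not confirm that these sources hold length of stay, so this must be checked first. Cost data will also be more variable and more skewed once newborn care is included.

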### Process evaluation

The data collected for the process evaluation include e.g. the number of participating women in each clinic, participation rate among all invited women, drop out rate, number of returned questionnaires in the study and participation rate in the monthly thematic meetings on physical activity. Information on reasons for non-participation was enquired from those women who refused to participate.

Information on the feasibility of the counseling was collected by structured telephone interviews to the nurses of the trial clinics after the trial. The interview included questions on perceived pros and cons related to the contents and procedure of counseling and data collection as well as the nurse's willingness to utilize the approach in their work. The questions were tested in the pilot study and modified for this purpose.

### Power calculations and sample size

The randomization of maternity clinics as clusters instead of women as individuals was taken into account in the power calculations [66]. When planning the RCT, no published studies on prevention of GDM among women at risk or data on decrease in the incidence of GDM were available. The power calculations for pair-matched study were based on the assumption of detecting a 40% reduction of incidence of GDM from 40% in the control clinics to 24% in the trial clinics. The power of the study was 0.80, significance level 0.05 and coefficient of variation of rate between clusters, indicating cluster sampling, 0.1. The dropout rate during the study (estimated 25%) was taken into account in the sample size calculations. Thus, a total number of 560 women should be recruited to the study. The number of women in the end of the study would thus be 210 + 210 (7+7 clinics, 30 women/clinic).

Success in recruitment and proportion of drop-outs (25%) were estimated based on the pilot study [28,67]. Our recruitment target seemed feasible since the annual number of deliveries in Pirkanmaa region was approximately 5000 [31] and at least fourth of these women were estimated to fulfill the inclusion criteria of this study.

The sample available for the 1-year follow-up (n = 462) is adequate to discover 5-20% difference of metabolic syndrome in trial and control groups. Intracluster correlation coefficient in the current study is estimated as 0.12 (valid when 0.10-0.30) [68].

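### The power section carries two unreconciled clustering assumptions (coefficient of variation 0.1 and ICC 0.12), and read as an ICC the second undercuts one of its two power claims

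*Protocol article*

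**What the plan says.** All of this is in the protocol article, under Power calculations and sample size.

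- First paragraph, GDM: the calculation treats the design as pair-matched, and the target effect is a fall in GDM incidence from 40% (control) to 24% (trial). It aims for 80% power at a 5% significance level. The clustering input is a "coefficient of variation of rate between clusters, indicating cluster sampling, 0.1". The analysed sample is "210 + 210 (7+7 clinics, 30 women/clinic"). With 25% dropout, "a total number of 560 women should be recruited to the study".
- Third paragraph: the 1-year follow-up sample of 462 women is called adequate for a difference of 5 to 20% in metabolic syndrome between the groups. The next and last sentence is "Intracluster correlation coefficient in the current study is estimated as 0.12 (valid when 0.10-0.30"). It has its own citation.

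The section does not link the two clustering figures. It does not say which outcome the ICC belongs to, whether it is at municipality, clinic or nurse level, or whether it is before or after pair-matching.

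**The concern.** A coefficient of variation and an ICC are two scales for the same thing, the spread of true rates between clusters. For a proportion each converts into the other. On the GDM scale the two stated values are far apart: one implies almost no clustering, the other heavy clustering. With only 14 municipalities, the clustering assumption largely decides the power.

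A GDM result that shows no difference will be read against a claimed power of 0.80. A metabolic syndrome result that shows no difference will be read against a statement that the sample was adequate. If the ICC is meant as written, at least one of these statements gives the reader too much assurance.

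**Working it through.** **Inputs from the protocol article.** p0 = 0.40, p1 = 0.24, difference d = 0.16; 7 pairs; m = 30 women analysed per cluster; power 0.80; alpha 0.05; k = 0.1; ICC 0.12 (0.10 to 0.30); 462 women at 1 year.

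**Assumptions.** Two-sided alpha, equal cluster sizes, the same ICC in both arms, clustering at municipality level.

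**1. The plan's own figure.** Matched-pair cluster formula (Hayes-Bennett), clusters per arm:

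c = 2 + (1.96 + 0.84)² × V / d², with V = [p0(1−p0) + p1(1−p1)]/m + k²(p0² + p1²)

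- V = (0.24 + 0.1824)/30 + 0.01 × (0.16 + 0.0576) = 0.01408 + 0.00218 = 0.01626
- c = 2 + 7.85 × 0.01626/0.0256 = 6.98, so 7 per arm
- Power with 7 pairs = Φ(√(5 × 0.0256/0.01626) − 1.96) = Φ(2.806 − 1.96) = 0.801
- 2 × 7 × 30 = 420, and 420/0.75 = 560

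Every primary figure reproduces.

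**2. One scale.** ICC = k² p/(1−p).

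- k = 0.1 at 40%: 0.01 × 0.4/0.6 = 0.0067. At 24% it is 0.0032.
- ICC 0.12 at 40%: k = √(0.12 × 0.6/0.4) = 0.42.
- Ratio on the ICC scale: 0.12/0.0067 ≈ 18.

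**3. If ICC 0.12 applies to GDM.** Design effect = 1 + 29 × 0.12 = 4.48, so 420 women carry the information of about 94. V = 0.4224 × 4.48/30 = 0.0631.

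- Same formula as in step 1: Φ(√(5 × 0.0256/0.0631) − 1.96) = Φ(1.425 − 1.96) = 0.30
- Paired t, 6 df: 0.295. Unpaired t, 12 df: 0.34
- Normal approximation without small-cluster correction (7 in place of 5): Φ(1.685 − 1.96) = 0.39
- Clusters per arm for 0.80: 2 + 7.85 × 0.0631/0.0256 = 21.3

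By the formula of step 1, the ends of the quoted range give 0.33 (ICC 0.10) and 0.16 (ICC 0.30).

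**4. If ICC 0.12 applies only to metabolic syndrome.** 462/14 = 33 per cluster. Design effect = 1 + 32 × 0.12 = 4.84, and 462/4.84 ≈ 95 effective women. The article gives no rates, so these are assumed. The range runs from the matched-pair formula to the uncorrected normal approximation.

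| Assumed rates | Power |
|---|---|
| 20% v 15% | 0.08 to 0.09 |
| 10% v 5% | 0.12 to 0.15 |
| 20% v 5% | 0.49 to 0.62 |
| 30% v 10% | 0.57 to 0.71 |

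**5. If 0.12 is really a coefficient of variation.** Step 1 with k = 0.12 gives a GDM power of 0.78, close to the stated 0.80.

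**6. Sensitivity of the 0.80.** Step 1 with k = 0.1, 0.2 and 0.3 gives 0.80, 0.66 and 0.50.

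**7. Can pair-matching close the gap?** Take 0.12 as the unmatched ICC and let matching remove a share r of the between-cluster variance. Power is 0.44 at r = 0.50, 0.73 at 0.90, 0.79 at 0.95 and 0.80 at 0.96.

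**The case against.** The strongest reply is that the two figures need not describe the same quantity. ICCs are specific to an outcome. The 0.12 comes directly after the metabolic syndrome sentence, in another paragraph from the GDM sizing and with its own citation. By position it belongs to a different outcome, time point and sample. This stands, so a strict contradiction is not shown. A reader might infer that the GDM power is really 0.30 and not 0.80, but the article does not support that without the condition that 0.12 applies to GDM.

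The reply does not clear the section. The ICC sentence speaks of the study as a whole and names no outcome. If it is confined to metabolic syndrome, the adequacy claim for that outcome fails at its lower end (step 4).

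A second reply is that k in a matched-pair formula is variation within pairs, whereas an ICC may be the total, and that pairs were matched partly on estimated GDM incidence. This is fair as to scale. But matching would have to remove about 95% of the between-cluster variance, and nothing in the article suggests that.

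Three further limits stand. The cluster level of the ICC is not stated. The meaning of the bracketed range 0.10 to 0.30 is unclear, so the power of 0.16 at its upper end should carry little weight. And the result at ICC 0.12 depends on method, so a range is the honest statement.

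**Conclusion.** The point holds as a failure to reconcile two stated assumptions. It is not an arithmetic error in the GDM sizing, where 7 clusters per arm, power 0.80 and 560 women all follow from the inputs given.

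Three readings of the 0.12 are open, and each needs a correction:

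- It covers GDM: power for 40% v 24% is about 0.30 to 0.39, and the stated 0.80 does not hold.
- It covers only metabolic syndrome: 0.80 stands on its own inputs, but power for a 5-point difference is about 0.08 to 0.15 at the assumed rates, so adequacy across the whole 5 to 20% range does not hold.
- It is a mislabelled coefficient of variation: GDM power is about 0.78, and the label is wrong.

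The article does not allow a choice between them. The sizes rest on the assumptions listed with the calculation, and for metabolic syndrome on assumed rates.

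**What to change.** - For each clustering figure, state the outcome, the scale (coefficient of variation or ICC), the cluster level, and whether it is before or after matching. If 0.12 is a coefficient of variation, relabel it.
- Restate the power claim that is affected. For GDM, give a range in place of the single 0.80: 0.80, 0.66 and 0.50 at k = 0.1, 0.2 and 0.3, and about 0.30 to 0.39 at ICC 0.12 if that value applies. For metabolic syndrome, give the assumed rates and the difference that 462 women in 14 clusters can detect under the stated ICC.
- Report the observed between-municipality variation in GDM with the primary result, so that a finding of no difference can be judged against the clustering that occurred.

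The cost is a few restated sentences and a less favourable stated power. No further enrolment is needed, and neither the design nor the analysis changes.
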